## Methods/ design

This study is designed as a multicenter, randomized phase II/III trial. The first step is a non-comparative randomized phase II trial. Its main objective study is to assess the efficacy of HAI oxaliplatin plus systemic fluoropyrimidine (LV5FU2 regimen) after curative-intent surgery (resection and/or thermal ablation) of at least 4 CRLM. Depending on the results, this randomized phase II study will be expanded into a phase III study to demonstrate the superiority of adjuvant HAI chemotherapy compared to systemic chemotherapy. The phase III will include the patients of the phase II and an additional group of patients to reach the total sample size needed for the phase III. If confirmed, this will have a clinically relevant impact on patient survival and an impact on public health because of the frequency of CRLM.

### Study objectives and endpoints

#### Primary objective

For the phase II, the primary objective is to assess the efficacy of HAI oxaliplatin plus systemic fluoropyrimidine (LV5FU2 regimen) after curative-intent surgery on 18-month hepatic recurrence-free survival (RFS) in patients at high risk of hepatic recurrence, meaning after resection and/or thermal ablation of at least 4 CRLM.

For the phase III, the primary objective is to demonstrate the superiority of adjuvant HAI oxaliplatin plus LV5FU2 compared to systemic oxaliplatin plus LV5FU2 (FOLFOX) on RFS in the same population.

#### Secondary objectives

The secondary objectives for phase II and III are based on the assessment of:the feasibility of delivering at least 4 cycles of HAI (or IV) oxaliplatin after surgical treatment of at least 4 CRLM.the toxicity of adjuvant HAI or of systemic chemotherapy after surgical treatment of at least 4 CRLM, including HAI catheter-related complications.the efficacy of adjuvant HAI plus LV5FU2 on RFS and OS and on the pattern of failures.

Hepatic RFS will be measured from the date of randomization to the date of hepatic recurrence, the date of other recurrences in the absence of hepatic recurrence as first event, the date of death whatever its cause in the absence of recurrence, or the date of last follow-up if the patient is alive. Non-hepatic recurrence as first event will be censored. RFS and OS will be measured from the date of randomization. For OS, the delay to the date of death, regardless of the cause, or to the date of last follow-up for patient alive will considered. For RFS, the delay to the date of recurrence, or death, regardless of the cause, or to the date of last follow-up for patient alive without recurrence will considered.

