### Statistical considerations

#### Required number of patients

The phase II is based on a two-step optimum Simon design [52] for the experimental arm, with the same number of patient in the control arm. The control arm allows checking that patients included are comparable to those included in previous studies that led to build study hypotheses, and to expand this study in a Phase III study by using a phase II-III design, depending on the study results.

The hypotheses are the following:18-months hepatic RFS rate with the control treatment of 30%18-months hepatic RFS rate with the experimental treatment of 50%A minimum follow-up time of 18 months for patient alive without recurrence.

With this hypothesis and to have a 95% power (beta risk = 5%) and a one-sided alpha risk of 10%, a total of 108 patients will have to be randomized. Since 5% of patients will be non-evaluable, a total of 114 patients will be included. The rate of non-evaluable patient will be monitored and if necessary an increase in sample size will be proposed. After the inclusion of the first 30 evaluable patients, an analysis on safety and feasibility after 6-month follow-up will be performed and reported to the independent data monitoring committee (IDMC).

An interim efficacy analysis in both arms will be performed after the inclusion of the first 30 evaluable patients with a minimum of 18-month follow-up in the experimental arm as planned by the Simon design. This analysis will be reported to the IDMC. Among the first 30 evaluable patients in the experimental arm,If 7 on the experimental arm or fewer patients were free of hepatic recurrence at 18 months, the Phase II will be stopped because of poor efficacy and the trial will be stopped.If 8 or more patients on the experimental arm were free of hepatic recurrence at 18 months, the Phase II will continue and the Phase III (or its activation) will be continued.

After evaluation of 18-month RFS in 54 evaluable patients,if 20 or less patients out of the 54 of the experimental arm were free of hepatic recurrence, the trial will stop because of poor efficacy.Otherwise, the conclusion will be that the 18-month RFS is good enough to continue or open to accrual the Phase III study.

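### The phase II go/no-go count does not match the endpoint behind its 30%/50% hypotheses and gives patients censored for extrahepatic relapse no defined status, so the 10%/95% error rates are not assured

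*Protocol article*

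**What the plan says.** All references are to the protocol article.

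- **Endpoint (Secondary objectives).** Hepatic RFS runs from randomization to hepatic recurrence, to another recurrence that comes first, or to "the date of death whatever its cause in the absence of recurrence". One of these end dates is then singled out: "Non-hepatic recurrence as first event will be censored". In the same section, overall RFS treats any recurrence or death as an event.
- **Design (Required number of patients).** "The phase II is based on a two-step optimum Simon design [52] for the experimental arm". Both hypotheses are labelled as 18-month hepatic RFS rates, 30% and 50%. The stated operating characteristics are "95% power (beta risk = 5%) and a one-sided alpha risk of 10%, a total of 108 patients will have to be randomized", raised to 114 for 5% non-evaluable patients.
- **Decision rule (same section).** Stage 1 stops the trial if 7 or fewer of the first 30 evaluable experimental-arm patients are free of hepatic recurrence at 18 months. The final step is introduced as an evaluation of 18-month RFS in 54 evaluable patients. The trial stops "if 20 or less patients out of the 54 of the experimental arm were free of hepatic recurrence"; otherwise "the conclusion will be that the 18-month RFS is good enough to continue".
- **Follow-up and analysis set.** The 18-month minimum follow-up is required for patients alive without recurrence (Required number of patients). The phase II analysis covers all randomized patients (Statistical analysis plan).

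**The concern.** One decision is described through three outcomes that differ for the same patient:

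| Patient by month 18 | Hepatic RFS as defined | Free of hepatic recurrence, read literally | RFS as defined |
|---|---|---|---|
| Hepatic recurrence first | event | failure | event |
| Extrahepatic recurrence first, liver clear | censored | success | event |
| Death without recurrence | event | success | event |
| Alive, no recurrence | no event | success | no event |

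The second row matters most. Censoring is meaningful for a survival curve, but a Simon rule adds up successes among a fixed number of patients and has no cell for a patient whose status is unknown. Whoever applies the rule must choose how to class these patients, possibly after the results are known. The choice can turn a stop into a go or the reverse, and a go commits 106 further patients.

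Censoring also affects the planned hepatic RFS rates. Extrahepatic-first relapse is a competing event, so a Kaplan-Meier rate that censors it need not equal the proportion of patients that the rule counts.

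**Working it through.** **Inputs.** p0 = 0.30, p1 = 0.50, n1 = 30 with stop at 7 or fewer, n = 54 with stop at 20 or fewer (Required number of patients).

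**Formula.** With X ~ Bin(30, p) and Y ~ Bin(24, p) independent,

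P(go | p) = sum over x = 8 to 30 of P(X = x) × P(Y ≥ 21 − x).

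**Step 1: the plan's own figures.** With every patient classed success or failure on the definition behind 30%/50%:
- alpha = P(go | 0.30) = 0.102, against a stated 10%
- power = P(go | 0.50) = 0.961, against a stated 95%
- 108 / 0.95 = 113.7, so 114, as stated

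The rule performs about as described when one definition applies throughout.

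**Step 2: how many patients could be affected.** The article gives no 18-month share of extrahepatic-first relapses. The sponsor's retrospective series gives 3-year hepatic DFS of 49% (HAI) and 21% (i.v.), and 3-year DFS of 33% and 5% (Adjuvant HAI of chemotherapeutic agents in high-risk patients). The gap is 49 − 33 = 16 points and 21 − 5 = 16 points. Because this is a 3-year gap and the series' definition of hepatic DFS is not given, the share q by 18 months is assumed to be 5, 10 or 16 points.

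**Step 3: effect of the classification on the printed rule.**

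(a) Counted as successes on top of p0 or p1, so the success probability is p + q.
(b) Counted as failures although the hypothesis had not counted them so: p − q.
(c) Dropped and replaced, with p the success share of all patients: p / (1 − q).
(d) Dropped and not replaced, cut-offs kept, with p the success share among those left: p × (1 − q) per enrolled patient.

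| Handling | q = 5 points: alpha / power | q = 10 points | q = 16 points |
|---|---|---|---|
| (a) successes | 31.9% / 99.4% | 61.5% / 99.9% | 88.1% / >99.9% |
| (b) failures | 1.7% / 85.0% | 0.1% / 61.5% | <0.1% / 26.5% |
| (c) dropped, replaced | 15.6% / 98.4% | 23.2% / 99.5% | 35.9% / 99.9% |
| (d) dropped, not replaced | 6.4% / 92.0% | 3.8% / 85.0% | 1.8% / 72.3% |

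For example, (a) at q = 5 points is P(go | 0.35) = 0.319, and (b) at q = 5 points is P(go | 0.45) = 0.850. In (d) at q = 10 points the success probabilities are 0.27 and 0.45.

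Even 5 points, no more than the plan's own non-evaluable allowance, moves alpha to between 1.7% and 31.9% and power to between 85.0% and 99.4%.

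**The case against.** **The error rates may be right.** If the hypotheses and the count share one definition, the rule gives 10.2% and 96.1%. In particular, stage 1 asks for liver status at 18 months. If the hepatic hazard is unchanged after an extrahepatic relapse, the share free of hepatic recurrence under the null stays at 30% and alpha at 10.2%. This stands: a reader might infer that the error rates fail, but the article shows only that they are not assured. The error can go in either direction.

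**Deaths.** A reader might infer that patients who die are counted as successes. Only the literal wording of the rule says so. The endpoint definition makes death without recurrence an event, and the hypotheses carry the hepatic RFS label. For deaths, one clarifying sentence is enough.

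**18-month RFS is probably a dropped word.** The abstract, the primary objective and the hypotheses all say hepatic. That is plausible, but correcting the word still leaves the extrahepatic-first patients without a status.

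**Non-evaluable patients are provided for.** The rate is to be monitored and the sample size raised if needed. This answers the shortfall in (d), but not the shift in success probability in (c).

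**Bias towards HAI.** A reader might infer that lower systemic exposure makes extrahepatic relapse more common in the HAI arm, so that hepatic events are hidden there. The only data in the article point the other way. If hepatic DFS in the series was censored as in this protocol, the 3-year cumulative extrahepatic hazard is ln(0.49/0.33) = 0.40 with HAI and ln(0.21/0.05) = 1.44 with i.v. treatment. The phase II is also non-comparative, so a difference between arms does not drive its decision.

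**Conclusion.** The point holds as an unresolved contradiction in the phase II decision rule. It does not rest on detail that an article leaves to the full protocol: the endpoint definition, the count and the conclusion are all printed, and they disagree. The stated 10% and 95% are not assured until one binary definition is fixed and the hypotheses are tied to it.

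The size depends on an assumed 5 to 16 points of extrahepatic-first relapse by 18 months and on how those patients are classed. Alpha runs up to 32%, 61% or 88% if they count as successes on top of 30%. Power falls to 85%, 61% or 27% if they count as failures against 50%. The 16-point end is a 3-year gap carried to 18 months and should be read as an upper illustration. The lower end already changes the design materially, so this should be settled before the first efficacy look.

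**What to change.** 1. Use one binary phase II endpoint in Primary objective, Secondary objectives and Required number of patients: alive and without hepatic recurrence at 18 months from randomization. Death from any cause is a failure.
2. For this count, do not censor extrahepatic-first patients. Classify them on liver status up to 18 months, and state how a patient lost before 18 months counts.
3. Replace 18-month RFS in the decision rule with this endpoint.
4. State that 30% and 50% refer to this endpoint, or restate them with the resulting alpha and power. Without this step, the new definition could carry the same mismatch.
5. Report the cumulative incidence of hepatic recurrence, with extrahepatic-first relapse and death as competing events, beside overall RFS.

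**Cost.** Mainly wording. Table 1 already schedules thoraco-abdomino-pelvic CT every 3 months for the first three years, so no scan is added, but the 18-month follow-up requirement must also cover patients with an extrahepatic relapse. The downside is that treatment of an extrahepatic relapse may influence later liver status; the competing-risk presentation shows how many patients this concerns.

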### Study population

This study will include patients after R0/R1 resection and/or thermal ablation of at least 4 CRLM (histological confirmation for at least one metastasis) without extrahepatic disease (except ≤3 lung nodules < 10 mm on chest CT scan deemed amenable to curative-intent resection/ablation).

Patients to be included in the study must fulfill the following inclusion criteria: histologically confirmed stage IV CRC, curative-intent R0/R1 resection (or thermal ablation) of at least 4 CRLM, preoperative oxaliplatin- and/or irinotecan-based chemotherapy +/− non-experimental biological therapy (e.g., anti-EGFR or antiangiogenic agent), confirmed radiological tumor control before surgery (i.e., objective response or stable disease according to RECIST1.1), age > 18 years, good health status (WHO performance status 0–1), adequate hematological function (absolute neutrophil count > 1.5 × 10^9^/l, platelets > 100 × 10^9^/l, hemoglobin > 9 g/dl), adequate liver function (serum bilirubin < 1.5 x ULN; alkaline phosphatase and transaminases < 5 x ULN), serum creatinine < 1.5 x ULN, informed consent signed by the patient or his/her legal representative, no pregnancy or breast feeding, adequate contraception in fertile patients, adequate private or national insurance coverage. Exclusion criteria include: extrahepatic tumor disease (except ≤3 lung nodules ≤10 mm on chest CT scan deemed amenable to curative-intent resection/ablation), symptomatic primary tumor requiring urgent surgery, contraindication to fluoropyrimidines or oxaliplatin, disease progression under oxaliplatin (including early hepatic relapse (less than 6 months) after end of adjuvant FOLFOX following primary tumor resection), history of any HAI treatment (chemotherapy, radioembolisation…), peripheral neuropathy> grade 1, history of cancer within 5 years prior to entry into the trial other than adequately treated basal-cell skin cancer or in situ carcinoma of the cervix, concomitant medications/comorbidities that may prevent the patient from receiving study treatments, patient already included in another clinical trial with an experimental molecule, patients unable to undergo medical monitoring test for geographical, social or psychological reasons.

An asymptomatic primary tumor is not a non-inclusion criterion if its resection is planned (reverse strategy allowed).

### Treatment schedule

Randomization will be either performed during surgery, or within 6 weeks after surgery using web-based procedure (TenAlea®). Adjuvant chemotherapy must begin within 8 weeks after surgery. Patients will be randomly assigned using minimization procedure in a 1:1 ratio to:Arm A (control arm): adjuvant systemic (i.v.) chemotherapy (FOLFOX) administered every 14 days:Oxaliplatin 85 mg/m^2^ in 2 h IV day (D)1,Folinic acid 400 mg/m^2^ in 2 h IV (concomitantly to oxaliplatin) D1, followed by5FU bolus 400 mg/m^2^ in 5–10 min IV D1 followed by5FU 2400 mg / m^2^ IV in 46 hArm B (experimental arm): adjuvant HAI chemotherapy plus systemic chemotherapy (LV5FU2) administered every 14 days:Oxaliplatin 85 mg/m^2^ in 2 h HAI D1,leucovorin 400 mg/m^2^ in 2 h IV (concomitantly to oxaliplatin) D1, followed by5FU bolus 400 mg/m^2^ in 5–10 min IV D1 followed by5FU 2400 mg / m^2^ IV in 46 h

Randomization will be stratified according to the following factors:Tumor response to preoperative chemotherapy (objective response vs. stable disease)Number of resected CRLM (4–8 vs. > 8)Center

Patients will receive adjuvant chemotherapy (HAI or systemic) for a maximal duration of 6 months and at least 3 months for the postoperative period. The minimal duration of chemotherapy (pre- and postoperative period) will be of 6 months. Before starting adjuvant chemotherapy, CT scan of the abdomen, pelvis and chest and serum tumor markers will be done (within 4 weeks before starting adjuvant chemotherapy). In both arms, continuation of targeted therapy (if any) used in the preoperative treatment will be allowed.

The HAI catheter will be placed before initiating treatment, either surgically or percutaneously by interventional radiology and bound to an implantable port. Angiographic and/or scintigraphic verification of the HAI catheter functionality will be done within 28 days before the start of treatment. HAI chemotherapy should be performed by physicians and nurses familiar with this technique.

### Assessments and follow-up

Follow-up will include every 3 months for the first 3 years following surgical procedure (months 3 to 36) and twice a year for at least 2 years (months 42 to 60), and then once a year for 3 years. For each visit, the assessments described in Table 1 should be performed. To study long-term effect on OS, patients will be followed for at least 3 years. A clinical study report will be issued for the 3-year RFS study (see statistical analysis for timing).

**Table 1 Tab1:** Plan of the study

VISITS	PRE-RANDOMIZATION WORKUP (maximum 1 month before)		Randomization	Follow-up during treatment					Follow-up		
				Every 2 weeks, during at least 3 months					The first three years : every 3 months	From 4 th to 5 th year : every 6 months	From the 6 th year to the8th : Every year
Visits N° Dates (days (D), months (M))	D-28 to D0	D-7 to D-1	D0	V1	V2	V3	V4	Vn	M 3, M6, M9, M12,....	M43, M49, M55, M61	
Informed consent signed	X										
Inclusion/Exclusion criteria		X									
Surgery			X ^c^								
TREATMENT											
- Oxaliplatine IAH or IV				X	X	X	X	X			
- LV5FU2 IV				X	X	X	X	X			
CLINICAL EXAMINATION											
- Weight, BMI, OMS statut		X		X	X	X	X	X	X	X	X
- Treatment toxicity				X	X	X	X	X	X		
EXAMS											
- Thoraco-Abdomino-pelvic CT scan^d^	X								X	X	X
- Electrocardiogram (ECG)		X									
- Control of the arterial catheter^a^				Every 8 weeks or more frequently if deemed necessary by the physicians							
LABORATORY EXAMS^b^											
- NFS-platelets	X			X	X	X	X				
- PT, INR	X										
- Ionogram, urea, creatinin level, liver biology	X	X		X	X	X	X				
- ACE, CA 19-9	X								X	X	X
- Pregnancy test	X										

^a^radiological ou angioscintigraphy

^b^liver biology: transaminases, alcalin phophatase, gamma glutamyl transferase, bilirubin Within 4 weeks before starting adjuvant chemo

^c^Patients are randomized peroperatively or within 6 weeks after surgery

^d^completed by MRI and/or Petscan according to the physician

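### The visit schedule runs from surgery in the text and from randomization in Table 1, while hepatic RFS runs from randomization; if the text is followed, phase II 18-month status is read up to 1.4 months early

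*Protocol article*

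**What the plan says.** All references are to the protocol article.

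- **Endpoint origin** (Secondary objectives): "Hepatic RFS will be measured from the date of randomization to the date of hepatic recurrence", and likewise "RFS and OS will be measured from the date of randomization".
- **Gap between surgery and randomization** (Treatment schedule): "Randomization will be either performed during surgery, or within 6 weeks after surgery". Footnote c of Table 1 repeats this.
- **Visit origin in the text** (Assessments and follow-up): "Follow-up will include every 3 months for the first 3 years following surgical procedure (months 3 to 36"). Table 1 places the thoraco-abdomino-pelvic CT at these visits.
- **Visit origin in Table 1** (same section): D0 is the column headed Randomization, and M3, M6, M9 and so on follow it. Surgery is marked in that same column, although footnote c allows a gap. The later visits are "M43, M49, M55, M61", one month after the months 42 to 60 given in the text.
- **Use of the endpoint** (Required number of patients): the experimental arm stops at 7 or fewer of 30, or at 20 or fewer of 54, free of hepatic recurrence at 18 months. The hypotheses are 30% and 50%, with one-sided alpha 10% and power 95%. At least 18 months of follow-up is required, with no origin given. The origin behind the 30% and 50% rates is not given either.
- **No test in phase II** (Statistical analysis plan): the arms are not formally compared at that stage.

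**The concern.** A recurrence found by imaging is normally dated at the scan that shows it. If scans run from surgery and the endpoint clock starts up to 6 weeks later, the month-18 scan falls before 18 months on the endpoint clock. A liver recurrence that develops between that scan and 18 months is then usually found at the following visit and dated after 18 months, so the patient counts as a success.

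Randomization cannot precede surgery, so the offset is either zero or early, never late. In a randomized comparison with a shared schedule it would largely cancel. In phase II it does not, because the decision rests on an absolute count in one arm against fixed cut-offs. The 18-month minimum follow-up is no safeguard, since it does not require a scan at or after 18 months from randomization. What is at stake is a modest rise in the probability of proceeding to phase III with a treatment that is no better than the null.

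**Working it through.** **Inputs.** Cut-offs 7/30 and 20/54, p0 = 0.30 and p1 = 0.50 (Required number of patients). Gap 0 to 6 weeks (Treatment schedule). Visits every 3 months (Assessments and follow-up). Two inputs are assumptions, because the article does not give them: a constant hazard, and the distribution of the gap. The calculation also takes the 30% null as measured from randomization.

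**1. The printed rule.** Exact two-stage binomial:

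P(go | p) = Σ over x = 8 to 30 of Bin(x; 30, p) × P[Bin(24, p) ≥ 21 − x]

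This gives 0.102 at p = 0.30 and 0.961 at p = 0.50. The 95% power is met, and the 10% alpha is met only approximately. The baseline for what follows is therefore 10.2%.

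**2. Scan times on the endpoint clock.** Six weeks = 42/30.44 = 1.38 months. For a patient randomized at 6 weeks, with visits counted from surgery:

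- month-18 scan: 18 − 1.38 = 16.62 months after randomization
- month-21 scan: 21 − 1.38 = 19.62 months

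For a patient randomized during surgery, the month-18 scan falls at 18.0 months.

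**3. Effect on the rate read.** With constant hazard and gap d, the rate read is p(18)^((18 − d)/18). At d = 1.38:

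- null: 0.30^(16.62/18) = 0.329
- alternative: 0.50^(16.62/18) = 0.527

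Averaging over the gap and putting the result into the formula of step 1:

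| Gap from surgery to randomization | Null rate read | P(go) under the null |
|---|---|---|
| None, or visits run from randomization | 30.0% | 0.102 |
| Half during surgery, half uniform over 0–6 weeks | 30.7% | 0.124 |
| All uniform over 0–6 weeks | 31.4% | 0.150 |
| All at 6 weeks (upper bound) | 32.9% | 0.212 |

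**4. Sensitivity to the hazard.** With a falling hazard (Weibull shape 0.6, assumed), the upper bound becomes 0.30^((16.62/18)^0.6) = 31.7%, and P(go) = 0.162.

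**5. A tempting remedy, checked.** One could keep surgery-timed scans and count a patient as free only on the first scan at or after 18 months from randomization. For any gap d above zero that is the month-21 scan, at 21 − d months, which is between 19.6 and 21 months. The wait beyond 18 months is 3 − d months, or about 7 to 13 weeks. With uniform gaps the rates read become 25.7% (null) and 45.7% (alternative), P(go) under the null falls to 0.023, and power falls from 0.961 to 0.874. With half the patients randomized during surgery, power is 0.927. This replaces an upward error of 1.4 points in the null rate (uniform gaps) with a downward one of about 4 points in both rates.

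**The case against.** The best reply is that this is an editorial slip. Table 1 sets D0 at randomization, and if sites follow the table there is no shift at all. That stands. A reader might infer that recurrence scans are definitely timed from surgery, but the article supports only that its text and its table disagree.

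Second, a reader might infer that the false-go probability doubles. The 21% needs every patient to be randomized at exactly 6 weeks, whereas the article expressly allows randomization during surgery. It also needs a constant hazard, and it applies the shift to every event, although deaths are dated when they occur. It is an upper bound and not an estimate.

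Third, the origin of the 30% and 50% rates is not stated. If they were measured from surgery, a status at month 18 from surgery would match them and the inflation against the null would disappear, although the status would still not match the endpoint definition. This stands as a condition on the result.

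Fourth, a reader might infer bias in phase III. Both arms share the schedule and the primary comparison is a log-rank test, so only the absolute 3-year rates would move (month-36 scan at 36 − 1.38 = 34.6 months at the latest randomization).

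Finally, visit windows and dating rules commonly sit in the full protocol or the analysis plan, which are not shown. Their absence is no finding. The contradiction about the origin is in the printed text.

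**Conclusion.** The point holds as an internal contradiction with a limited effect in one direction. The follow-up text, Table 1 and the endpoint definition do not share one time origin. If the text governs, phase II status at 18 months is read up to 1.4 months early, in favour of go. For plausible mixes of randomization times the null rate is read as 30.7% to 31.4%, and P(go) is 12% to 15% instead of 10.2%; the upper bound is 32.9% and 21%. These figures assume a constant hazard, recurrences dated at detection, and a 30% null measured from randomization. The effect is zero if Table 1 governs or if all patients are randomized during surgery. Phase III is essentially unaffected. The correction is worth making because the error cannot run the other way and the remedy is cheap.

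**What to change.** 1. Reconcile the endpoint definition (Secondary objectives), the follow-up text and Table 1, so that outcome imaging and the endpoint share one origin, the date of randomization. In Table 1, separate surgery from D0 and align the later visits (M43 to M61) with months 42 to 60.
2. State that 18-month hepatic status is taken from the nominal month-18 scan, so that a scan a few days late does not move a recurrence past 18 months.
3. Confirm that the 30% and 50% rates are measured from the same origin. If they are not, say so and restate them.

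Do not combine surgery-timed scans with a rule based on the first scan at or after 18 months, because that can cut power to about 87%.

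The cost is wording only: no extra patients and no extra scans. For patients randomized after surgery, the nominal visit dates move by at most 6 weeks.
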